# Effects of Aerobic Training Versus Behavioral Intervention to Increase Physical Activity for Disease Control in Patients With Asthma: Protocol for a Randomized Trial

**DOI:** 10.2196/78603

**Published:** 2025-10-30

**Keywords:** asthma, physical activity, physical exercise, sedentarism, quality of life

## Abstract

**Background:**

Aerobic training (AT) and behavioral intervention (BI) aimed at increasing physical activity provide numerous benefits to patients with asthma. However, the comparison between the two interventions in the clinical control of this disease is poorly understood.

**Objective:**

This study aims to compare the effects of AT and BI on disease control in people with moderate to severe asthma.

**Methods:**

This is a randomized 2-arm clinical trial with a blinded evaluation. The study will include 56 physically inactive adults with uncontrolled asthma despite optimized medication. Eligible patients will be randomized into either the AT group or the BI group. AT will be performed on a treadmill for 8 weeks (2 sessions per week, 45 minutes each), and the intensity will be determined by the maximum heart rate established in the cardiopulmonary exercise test. BI will be based on social cognitive theory and behavioral change stages that will last 8 weeks (1 session per week, 90 minutes per session). All interventions will last a total of 12 hours. Assessments will be conducted pre- and postintervention and again 16 weeks later and will include physical activity in daily life (PADL; assessed using triaxial accelerometry) level, body composition (measured using octopolar bioimpedance), barriers to PADL (questionnaire), clinical asthma control (Asthma Control Questionnaire), quality of life (Asthma Quality of Life Questionnaire), anxiety and depression levels (Hospital Anxiety and Depression Scale), and number of exacerbations. Time and group interactions will be evaluated using 2-way repeated measures ANOVA. The significance level will be set at *P*<.05.

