## Methods

### Study Design

This study is a randomized trial with 2 parallel arms and a blinded evaluation. The study will be conducted at a university hospital that offers specialized treatment for moderate to severe asthma. The study protocol was developed in accordance with the SPIRIT (Standard Protocol Items: Recommendations for Interventional Trials) checklist guidelines [15], and the trial is registered at ClinicalTrials.gov (NCT05364632). The study flow diagram is presented in Figure 1.

After a regular medical visit, adult outpatients with asthma will be invited to participate in the study, and asthma pharmacotherapy will be maintained during the intervention. Initially, eligible patients will be randomized by a researcher not involved in the study using a computer-generated sequence into 2 groups: the AT group or the BI group. The total duration of each intervention for both groups will be 12 hours (720 minutes). Both groups will be evaluated before and after the interventions and again 16 weeks later. The evaluations will be carried out in a blinded fashion by an evaluator who will not be directly involved in the interventions.

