### Outcome Measures

The primary outcome will be to compare the effects of AT and BI to increase the PADL on clinical asthma control. The secondary outcomes will include quality of life, sleep quality, asthma exacerbations, anxiety and depression levels, barriers that hinder the practice of PADL, body composition, and anthropometric data.

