#### Asthma Exacerbation

Asthma exacerbation is defined as the patients’ need for urgent medical action and a change in pharmacological treatment [43]. During the study, at least one of the following criteria will be used to determine an exacerbation: the use of ≥4 puffs of rescue medication per 24 hours during a 48-hour period; the need for the administration of systemic corticosteroids (pills or injections); or unscheduled medical appointments, visits to the emergency room, or hospitalization [26,32,43].

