### Statistical Analysis Planning

The sample size calculation (n) was established based on the clinical control measured by the ACQ to detect a clinical improvement of 0.5±0.6 points [34]. The required sample size will be 24 patients per group for a total of 48 patients, and a 15% loss will be considered, resulting in a total of 56 patients. The sample power was considered 80% with a significance level of 5%. Before the interventions, clinical, anthropometric, physical fitness, PADL, and psychosocial data obtained at baseline will be compared using the 2-tailed *t* test or Mann-Whitney test (depending on data normality) for continuous variables. The chi-square test will be used to compare categorical variables. After the intervention, time and group interactions will be evaluated using a two-way repeated measures ANOVA. The significance level will be adjusted at *P*<.05 for all tests, and the SigmaStat (version 3.5; Systat Software) program will be used for statistical analysis. All the analyses will follow the intention-to-treat principles until 15% of the data are missing. For confidentiality, the participants will be given an anonymous study ID, and only the study investigators will have access to the final trial dataset.

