### Strengths and Limitations of the Study

This study protocol will be a randomized trial with a 4-month follow-up postintervention. It is essential to determine whether the possible gains will be maintained in the medium term following the intervention. Objective measures of physical activity and sleep quality (ActiGraph GT9X), physical fitness (CPET), and body composition (Octopolar InBody 720) are another strength of this study. One limitation is that assessments using questionnaires are considered subjective measures. However, all tools have been validated and are widely used in interventions for people with asthma. The fact that the study will be conducted in a single hospital center may represent another limitation.

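### Exacerbation counts go into a repeated measures ANOVA with no allowance for observation time; if counts run between visits, the time effect is an artefact, and the test between arms is weaker than it need be

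*Protocol article*

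**What the plan says.** Exacerbations are a secondary outcome: "The secondary outcomes will include quality of life, sleep quality, asthma exacerbations" (Outcome Measures). Table 2 ticks them at baseline, 8 weeks and follow-up.

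The abstract gives the outcome as a number of events and goes straight on to the method: "and number of exacerbations. Time and group interactions will be evaluated using 2-way repeated measures ANOVA". The section Statistical Analysis Planning repeats it: "After the intervention, time and group interactions will be evaluated using a two-way repeated measures ANOVA". Neither place mentions a rate, an exposure offset or a model for counts.

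On timing, the abstract says "AT will be performed on a treadmill for 8 weeks", and the BI also lasts 8 weeks. Study Design adds "Both groups will be evaluated before and after the interventions and again 16 weeks later". The strengths and limitations section agrees: "This study protocol will be a randomized trial with a 4-month follow-up postintervention".

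The Asthma Exacerbation section introduces its event criteria with "During the study, at least one of the following criteria will be used to determine an exacerbation". It does not say over what period events are counted at each visit, or how far back the baseline count reaches.

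**The concern.** A questionnaire score can be compared across visits as it stands. A number of events can be compared only if each visit's count covers the same length of time. The visits here are 8 and then 16 weeks apart, and the baseline look-back is a third, unknown period. If each count covers the time since the previous visit, raw counts move with window length even when no patient's risk changes.

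The time effect matters because the trial expects similar benefits in both arms (Objectives, for asthma control and quality of life) and wants to know whether gains persist (Conclusions). If the interaction is not significant, readers will look at change over time. For exacerbations that change could be produced by window length alone: a rise if the look-back is short, a fall if it is long.

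A second question is how well a group-by-time interaction on sparse counts answers what a randomised comparison asks, namely whether event rates after randomisation differ between arms.

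**Working it through.** **The plan's own figure.** None is given for exacerbations. The only sample size is for ACQ: difference 0.5, SD 0.6, 80% power, 5% level. The t-based two-sided calculation gives 23.6, so 24 per group (power 0.807), as stated. 48 × 1.15 = 55.2, rounded up to 56. This supplies 56 / 2 = 28 per arm below.

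**Inputs from the article.** Intervals of 8 and 16 weeks (visit spacing); 28 per arm; 5% level; two-way repeated measures ANOVA on three visits.

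**Assumptions, because the article gives no figures.** Counts run from visit to visit; 1, 2 or 4 events per patient-year; baseline look-back of 8 or 52 weeks; Poisson counts with gamma variation between patients, variance 1; where an effect is simulated, one arm's rate is halved after randomisation.

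**Step 1: expected counts at constant risk.** Mean count = annual rate × weeks / 52. At 2 per year:
- 8 weeks: 2 × 8 / 52 = 0.31
- 16 weeks: 2 × 16 / 52 = 0.62
- 52 weeks: 2.00

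The follow-up count is twice the 8-week count with no change in risk. With gamma variance 1, the share of patients with no event in 8 weeks is 1 / (1 + mean), which is 1 / 1.31 = 76%.

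**Step 2: rejection rates with no change in risk and no difference between arms** (simulation, 8-week look-back unless stated).

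| Events per year | Time effect, raw counts | Time effect, 52-week look-back |
|---|---|---|
| 1 | about 40% | about 100% |
| 2 | about 70% | about 100% |
| 4 | about 94% | about 100% |

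With the 52-week look-back the spurious change is a fall from baseline (2.00 to 0.31 and 0.62 at 2 per year). The same ANOVA on events per week rejects in about 5% to 6%. The group-by-time interaction on raw counts rejects in about 5%, rising to about 7% with a 52-week look-back.

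**Step 3: power when one arm's rate is halved.**

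| Events per year | Interaction, 8-week look-back | Interaction, 52-week look-back | t test on 24-week totals |
|---|---|---|---|
| 1 | about 12% | about 9% | about 22% |
| 2 | about 21% | about 10% | about 32% |
| 4 | about 36% | about 11% | about 46% |

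The t test keeps its size at about 5%, so the comparison is like for like. With gamma variance 0.5 the pattern is the same: 12%, 21% and 38% for the interaction (8-week look-back), against 23%, 40% and 60% for a quasi-Poisson rate comparison.

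**Step 4: where the power goes.** At 2 per year:
- Equal windows of 12, 12 and 12 weeks give interaction power of about 15%, below the 21% with 8, 8 and 16 weeks.
- ANOVA on rates repairs the time effect, but its interaction power is about 13%.
- A plain t test on post-baseline totals, with no rate adjustment, already reaches about 32%.

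So the loss comes from testing a group-by-time interaction on sparse counts with the baseline count as one of its levels. A long look-back makes it worse.

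**The case against.** The strongest reply is that the windows are inferred. The article gives visit spacing, not recall length. A fixed recall period at every visit is not excluded, and with equal periods the artefact in the time effect would vanish. The follow-up column of Table 2, labelled 16 weeks, could also be read as week 16 from baseline, though the abstract, Study Design and the limitations section all support 16 weeks after the intervention. This stands as a limit: the artefact is conditional on counting between visits. It does not clear the plan, because the text leaves the period open while fixing an analysis that works only if the periods are equal. Equal short recall would also leave part of the follow-up uncounted.

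A second reply is that the ANOVA sentence is generic and the model for each secondary outcome may sit in a fuller plan. That is fair for the statistics section, which names no outcome. The abstract, however, places the number of exacerbations immediately before the ANOVA, and no exception is made anywhere.

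Third, a reader might infer that the unequal windows bias the comparison of AT with BI or cost it power. Neither is supported. Both arms share the same visit schedule, the interaction keeps its size closely, and equal windows give less power, not more.

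Finally, the gain in power should not be oversold. Robust Poisson regression detected the halved rate in about 26%, 39% and 52% of simulated trials, but with an actual size of 6% to 7%. A permutation test with size 3% to 4% reached 15%, 30% and 42%, against 12%, 22% and 34% for the interaction in the same simulation: a gain of 3 to 8 points with an 8-week look-back.

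**Conclusion.** The point holds in this form. The article puts a count of events through a repeated measures ANOVA without stating the counting period or allowing for it. If counts run between visits, the time effect is an artefact of window length and cannot be interpreted: about 40%, 70% and 94% false significance at 1, 2 and 4 events per patient-year with an 8-week look-back, and near certainty with 52 weeks.

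The comparison between arms remains essentially valid but is weaker than a direct comparison of post-randomisation events. That weakness belongs to the choice of an interaction test on sparse counts, not to the window lengths.

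The percentages rest on assumed event rates, between-patient variation, look-back and effect. The doubling of the count rests only on the inferred 8- and 16-week windows. This is one secondary outcome; the primary ACQ analysis and the sample size are untouched. The change should be made, and can be made before analysis because data collection is still under way.

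**What to change.** In Statistical Analysis Planning:

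1. Take exacerbations out of the repeated measures ANOVA.
2. State the period over which events are counted at each visit, including the baseline look-back.
3. Compare arms on the number of events from randomisation to the follow-up visit by negative binomial regression, or Poisson regression with robust standard errors, with log(weeks observed) as offset. Report a rate ratio with 95% CI. Add a permutation P value because the sample is small and the robust Poisson test runs slightly above its nominal size.
4. Show rates per patient-week for each period as description only, with no test of change over time on raw counts.

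The offset also lets a patient who leaves early contribute the weeks actually observed, so that for this outcome the last available count need not be carried into a window of another length.

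The cost is a few sentences and software that fits count regression. No new data are needed if events are recorded over the whole of follow-up; if recall is shorter, the offset must be the weeks actually covered. The small downside is a wide interval for the rate ratio, so the result must be described as imprecise.

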**Results:**

As of October 2025, 52 participants had been recruited. This study was funded by the São Paulo Research Foundation and the National Council for Scientific and Technological Development. Clinical trial registration was granted in May 2022. Recruitment and data collection for the trial are ongoing, and the results of this study are expected to be available by the end of December 2026.

**Conclusions:**

This is the first study to compare the effects of AT versus BI on increasing physical activity for clinical asthma control. Therefore, the results obtained in the proposed protocol may provide essential information for health care professionals when recommending these approaches to people with asthma.

**Trial Registration:**

ClinicalTrials.gov NCT05364632; https://clinicaltrials.gov/study/NCT05364632

**International Registered Report Identifier (IRRID):**

DERR1-10.2196/78603

## Introduction

**Overview**

Asthma is a heterogeneous disease characterized by chronic airway inflammation [1]. It is defined by respiratory symptoms, including shortness of breath, wheezing, chest tightness, and variable expiratory airflow limitation [1]. It is a global problem, and its incidence and prevalence are increasing [2]. Asthma is the second most common chronic respiratory disease and affects approximately 300 million people worldwide [3]. In 2019, 262 million people were diagnosed with asthma, and 461,000 died from the disease [3].

Asthma control strategies include pharmacological and nonpharmacological treatments [1]. A structured and supervised aerobic exercise program, such as aerobic training (AT), is a nonpharmacological behavioral treatment known to improve asthma control [4-7]. Behavioral intervention (BI), aiming to increase physical activity in daily life (PADL), is also part of the nonpharmacological treatment [8]. Both interventions improve the patient’s quality of life and asthma symptoms and help minimize exacerbation episodes [7-9].

In 2020, the World Health Organization [10] recommended that adults perform 150 to 300 minutes of moderate-intensity aerobic physical activity weekly to achieve health benefits. People with asthma are less physically active than their healthy counterparts [11]; thus, developing strategies to modify behavior, increase physical activity, and reduce sedentary time among people with asthma is important [12]. Freitas et al [8] applied an 8-week BI to increase PADL and reported improvements in clinical asthma control, PADL, sleep quality, and anxiety symptoms in adults with moderate to severe asthma. Another effective strategy to improve the clinical control of asthma is the AT [13,14]. Furthermore, AT programs have been used as an intervention to reduce the exacerbation of asthma episodes and improve quality of life, making AT a treatment option [9].

**Objectives**

As previously mentioned, evidence suggests that AT or BI can improve asthma symptoms and reduce comorbidities. However, the comparison between these interventions in improving asthma control remains poorly understood. We hypothesize that these interventions will promote similar benefits in asthma control and quality of life in people with asthma. The main objective of this study is to compare the effects of AT versus BI in increasing physical activity for clinical asthma control. The secondary outcomes will include quality of life, physical activity level, sleep quality, asthma exacerbations, behavioral stages of physical activity, body composition, anthropometric variables, anxiety and depression symptoms, and cardiopulmonary exercise testing (CPET).

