## Discussion

### Potential Relevance and Impact of the Study

This randomized clinical trial, with 2 parallel arms and blinded evaluation, compares the effects of AT and BI on clinical control in individuals with moderate to severe asthma. The effects of physical exercise on people with asthma have been widely discussed in recent years [14], and physical exercise has been proposed as a nondrug therapy for asthma management. AT promotes anti-inflammatory effects in patients with asthma and improves exercise-induced bronchoconstriction [12]. In addition, physical training improves physical conditioning and health-related quality of life, and reduces bronchial hyperresponsiveness, the use of long-term bronchodilators and corticosteroids, and asthma symptoms [5,7,14,27,58,59]. BI, aimed at increasing PADL in people with asthma, also promotes better disease control [8]. Furthermore, recent studies have shown that a higher number of steps per day is associated with better clinical control of moderate to severe asthma [60], and that the minimum clinically significant difference is 1413 steps per day [61]. The results of this study may be highly relevant to clinical practice, as they will enable a similar understanding of how both interventions can improve clinical control of asthma in the short and medium term, regardless of the approach used.

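### The hypothesis is that the two interventions give similar benefit, but the plan sizes and tests only for a difference and sets no margin, so only a non-significant P value could support it

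*Protocol article*

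**What the plan says.** All references are to the protocol article.

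- **Objectives, hypothesis:** "We hypothesize that these interventions will promote similar benefits in asthma control and quality of life in people with asthma".
- **Objectives, aim:** "The main objective of this study is to compare the effects of AT versus BI in increasing physical activity for clinical asthma control". The aim is not labelled superiority, non-inferiority or equivalence.
- **Statistical Analysis Planning, sample size:** the calculation is made "to detect a clinical improvement of 0.5±0.6 points" on the ACQ, with 80% power and a 5% significance level. It gives 24 per group, 48 in all, raised to 56 to allow for 15% losses.
- **Statistical Analysis Planning, analysis:** "After the intervention, time and group interactions will be evaluated using a two-way repeated measures ANOVA", at P<.05 for all tests.
- **Primary Outcome: Asthma Clinical Control:** an ACQ change of 0.5 points or more is called clinically significant. It is not declared as a margin between arms.
- **Potential Relevance and Impact of the Study:** the results are expected to help show "how both interventions can improve clinical control of asthma in the short and medium term, regardless of the approach used".

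No section gives a similarity margin or a rule based on a confidence interval.

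**The concern.** Both arms are active and there is no untreated control. The expected finding is that they do about equally well. The planned test takes no difference as its null hypothesis, so it can produce evidence of a difference but not of similarity. If P is below .05, the hypothesis is contradicted. If it is not, the data may fit a negligible difference, a clinically significant one, or both, and the plan has no means of telling these apart.

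The headline conclusion on the primary outcome is at stake. Clinicians choosing between supervised training and a behavioural programme would act differently on *shown to be similar* and on *not shown to differ*. This is more than a detail that an analysis plan could fill in. The article itself fixes the hypothesis, the sample size and the test, and a similarity margin would be an input to the sample size.

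**Working it through.** **Inputs.** From Statistical Analysis Planning: difference 0.5, SD 0.6, power 80%, significance level 5% (taken as two-sided), 24 per group, 56 in total (28 per group if nobody is lost). From the primary outcome section: 0.5 points as the clinically significant change. The margins used in steps 4 and 5 are assumptions, because the article gives none.

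**1. Reproducing the stated size.** Normal approximation: n = 2 × [0.6 × (1.960 + 0.842) / 0.5]² = 22.6, so 23 per arm. The two-sample t test gives 23.6, so 24 per arm, with power 80.7%. For losses, 48 × 1.15 = 55.2, so 56. The plan's figures are reproduced. A one-sided 5% test would need only 18 to 19 per arm. A paired within-group calculation with the same inputs would need about 14.

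**2. Precision at that size.** The standard error is 0.6 × √(2/24) = 0.173. The 95% CI half-width is 2.013 × 0.173 = 0.35 and the 90% half-width is 1.679 × 0.173 = 0.29. With 28 per arm they are 0.32 and 0.27. As an illustration, an observed difference of 0.34 would be non-significant at 24 per arm, with a 95% CI of about −0.01 to 0.69.

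**3. Chance of a non-significant result** (two-sided t test at one time point, SD 0.6, 24 per arm):

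| True difference | P(non-significant) |
|---|---|
| 0 | 95% |
| 0.25 | 71% |
| 0.30 | 60% |
| 0.35 | 49% |
| 0.40 | 38% |
| 0.50 | 19% |

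**4. What a similarity rule would deliver.** Similarity is declared only if the whole CI for the difference lies within ± margin. The 90% CI corresponds to two one-sided tests at 5% each. Power when the true difference is 0 and the SD is 0.6:

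| Margin | CI | 24 per arm | 28 per arm |
|---|---|---|---|
| ±0.5 | 90% | 77% | 85% |
| ±0.5 | 95% | 61% | 73% |
| ±0.4 | 90% | 47% | 59% |
| ±0.3 | 90% | 8% | 17% |

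With margin ±0.5, the chance of wrongly declaring similarity at a true difference of 0.5 is held to 5% with the 90% CI, or 2.5% with the 95% CI. At 24 per arm, the observed difference would have to be within about 0.5 − 0.29 = 0.21 (90% CI) or 0.5 − 0.35 = 0.15 (95% CI).

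**5. Size needed for 80% power** under the 90% CI rule: n = 2 × [0.6 × (1.645 + 1.282) / margin]², which gives 25 per arm at ±0.5, 39 at ±0.4 and 69 at ±0.3. At ±0.5, an SD of 0.8 or 1.0 (assumptions) would raise this to 44 or 69.

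**6. How the two readings diverge.** At a true difference of 0 and 24 per arm, 95% of trials are non-significant, but only 61% have a 95% CI inside ±0.5. So about 1 − 0.61/0.95, roughly 35%, of non-significant results would still have a CI reaching 0.5 in one direction.

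**The case against.** The strongest reply is that the main objective is only to compare the interventions, which a two-sided difference test does, and that the similarity sentence merely records what the investigators expect. This stands in part. The trial can answer whether the arms differ, and it would be too strong to say that it cannot answer its question at all. What it cannot do, as planned, is support the hypothesis it states.

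Three stronger readings are tempting but not supported:

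- *A non-significant P value will be reported as similarity.* No section says so. The discussion sentence quoted above is loose prose about relevance, not a decision rule. The documents show only that the plan offers no other route to its hypothesis.
- *The figure of 24 per group proves a difference design.* It does not. A non-inferiority calculation with margin 0.5, SD 0.6 and one-sided 2.5% gives the same number (23 by the normal approximation, power 80.7% at 24). The design is shown by the stated aim to detect an improvement, the interaction test and the absence of any margin.
- *Dropout and carrying forward the most recent assessment must favour similarity.* This is unproven. Differential dropout can create a difference, carry-forward can understate variance, and a 15% loss is already allowed for.

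Two further objections are fair. The 19% at a true difference of 0.5 is simply the planned type II error, and becomes a problem only if a non-significant result is taken as support for similarity. And the figures describe a t test at one time point, whereas the planned ANOVA is a repeated-measures analysis of assessments before, after and 16 weeks later.

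**Conclusion.** The point holds: a hypothesis of similarity is paired with a sample size and a test for a difference, with no margin. On the plan's own SD of 0.6 and 24 per arm, a non-significant result is compatible with differences well above 0.5 points. It would occur in about half of trials at a true difference of 0.35 and in 71% at 0.25.

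The size of the problem depends on the margin and the SD. If ±0.5 can be justified, the planned 24 to 28 per arm come close to or exceed 80% power with a 90% CI (77% to 85%). At ±0.4 they do not (47% to 59%), and at ±0.3 the trial is far too small. These figures assume a true difference of zero, SD 0.6 and no baseline adjustment. The matter concerns the primary outcome and should be settled before results by arm are seen, because a margin chosen afterwards carries little weight.

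**What to change.** Before outcome data are examined by arm, state in the analysis section and the registry entry that P≥.05 does not support similarity. Commit to reporting the AT minus BI difference in ACQ at the end of the intervention with its confidence interval. Then choose one of two routes.

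**(a) Keep the similarity hypothesis.** Declare similarity only if the 90% CI (two one-sided tests at 5%) lies wholly inside a stated margin. Otherwise report a difference if one is shown, or an inconclusive result. The margin needs a justification. ±0.5 is a natural candidate because the article already calls that change clinically significant, but it is lenient as a between-arm margin. Restate the power for the chosen margin and CI level from the table above, and disclose that the margin was set late: the abstract reports 52 of the planned 56 recruited as of October 2025.

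**(b) Reword the hypothesis as a test for a difference,** keep the planned comparison, and draw no conclusion of similarity.

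Neither route needs more patients. Route (b) costs only wording. Route (a) is a late design change and must be reported as one. Its price is that an inconclusive result becomes a realistic outcome even if the arms are identical, and that stated power for the similarity claim may fall below 80%: 77% at 24 per arm with a 90% CI and ±0.5, and 61% if a 95% CI is used.
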